### Study objectives and contributions

This study has three primary objectives. The first objective is to assess the inter-method reliability of the rapid phone-based HFA compared to the comprehensive in-person HFA. This objective focuses on isolating the survey mode effect – the differences in results due to the phone and in-person administration – and will determine the extent to which phone data collection is a reliable alternative mode for conducting HFAs for a subset of key PHC service delivery indicators. To minimize bias, this objective will include only the survey questions that are identical in both the rapid phone-based HFA and the comprehensive in-person HFA. By keeping questions the same and varying only the administration mode, we can effectively isolate and examine the mode effect.

The second objective is to assess the concurrent criterion validity of indicators in the rapid phone-based HFA compared to indicators in the comprehensive in-person HFA. As discussed earlier, phone surveys require questions that are shorter, simpler, and less cognitively demanding. While this design is crucial for phone-based assessments, it can lead to issues such as questions being interpreted differently by respondents or lack of clarity or confusion on specific terms in the asked question that may affect data quality. This objective therefore focuses on evaluating the extent to which the rapid phone-based HFA can accurately measure the same underlying indicators as that in a comprehensive in-person HFA via a simplified questionnaire deemed suitable for phone-based administration.

The third objective is to compare the survey response rates and dropout rates of the rapid phone-based HFA to those of the comprehensive in-person HFA. Survey response rates are crucial for interpreting results and identifying potential biases. This is especially important for phone surveys where respondents can more easily drop out or refuse to participate in the survey. For instance, unlike for in-person surveys wherein respondents might feel more obligated to participate in a survey due to the physical presence of the interviewer, the respondents might find it easier to not answer a phone call or hang up. Additionally, phone surveys may also have higher non-response rates due to poor connectivity or time constraints faced by respondents.

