Following the mapping, a question-by-question revision activity was conducted to identify the two types of survey items mapped across both the questionnaires: (1) ‘direct’ survey items and (2) ‘indirect’ survey items. Survey items were categorized as ‘directly mapped’ when the framing and underlying indicator of the survey item were identical (or nearly identical) across both surveys. This required a one-to-one match of a question in the rapid phone-based HFA and the comprehensive in-person HFA. These survey items were commonly the ones wherein the comprehensive in-person HFA question structure was appropriate for phone administration. For instance, both surveys include the same question to identify the source of electricity at health facilities (‘What is the health facility’s main source of electricity?’). We also considered questions with identical wording across both surveys but which include enumerator verification through direct observation in the comprehensive in-person HFA “directly mapped”, because we consider in-person verification as a component of the mode effect. This includes questions on the availability and functioning of facility inputs, such as private toilets, where the enumerators in the comprehensive in-person HFA can verify the response due to being physically present in the health facilities. Directly mapped indicators will be included in objective one (reliability/mode effect) and objective two (validity) testing.

Survey items were classified as ‘indirectly mapped’ when they intended to measure similar underlying indicators in both surveys, but differed in the way they were asked or framed due to feasibility for phone administration. This typically occurred when comprehensive in-person HFA survey items were too lengthy or detailed to be administered over the phone, leading to simpler alternatives being included in the rapid phone-based HFA. For example, in measuring HIV/AIDS service provision, the rapid phone-based HFA asks whether the health facility provides HIV/AIDS services, while the comprehensive HFA asks whether the health facility was able to provide HIV/AIDS diagnosis services and HIV/AIDS treatment services in the 3 months prior to data collection. In this case, the underlying indicator “HIV/AIDS service availability” was common in both the surveys but was captured differently in each, leading to it being “indirectly mapped.”

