#### Data collection procedures.

Both surveys will involve comprehensive training for enumerators to familiarize them with survey protocols, questionnaire administration, and ethical considerations for each assessment. This will be followed by additional pilot testing the instrument in a few health facilities to identify any necessary changes and to provide enumerators with field experience before starting data collection.

At least one week before data collection commences, a data collection supervisor will contact the PHC network managers (individuals who manage several public health facilities) via phone to introduce themselves and both surveys. They will also request the names and contact information of the relevant sampled health facilities under their supervision. The PHC managers should have received the official notice from the Government regarding the surveys and that their facilities may have been included in the sample. If they do not have the official communication, the supervisor will share with them a copy of the official letter. PHC network managers will then be responsible for notifying officers-in-charge of sampled health facilities.

The rapid phone-based HFA is designed as a short 30–45 minutes survey, requiring no preparation by the officer-in-charge. Respondents will have the option to either start answering the survey during the first call, or to schedule it for a more convenient day or time. If a respondent is unreachable, the rapid-cycle survey protocol requires at least five contact attempts on different days and at varying times to complete the interview, maximizing communication success and reducing potential biases introduced by timing constraints. This will be particularly important for remote facilities with low phone connectivity, where the respondent may have sporadic access to a stable phone network. In instances where immediate completion of the interview is not feasible due to telecommunications issues or respondent availability, follow-up calls may be scheduled for a later date or time.

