For the comprehensive in-person HFA, enumerator teams will contact the officers-in-charge of sampled facilities two weeks before data collection, to inform them about the survey, coordinate the date of the first visit, and share the ‘advance questionnaire’. The advance questionnaire is a subset of the comprehensive in-person HFA and comprises of questions that require reference to facility data records. This will be shared with the officer-in-charges at least two weeks prior to data collection day, allowing respondents to prepare responses, thereby saving time and improving data quality on the day of data collection.

If facilities have not received the official communication about their participation in the survey, PHC managers will be contacted to ensure that all selected facilities receive the official letter requesting their participation. For the comprehensive in-person HFA, one week before data collection, enumerator teams will again contact the officers-in-charge to confirm the date of the first visit and request completion of the advance questionnaire. This follow-up will also provide an opportunity to address any questions the officers-in-charge may have about the survey and to reschedule the first visit, if necessary. Furthermore, if on the day of data collection, the facility is closed, or the officer-in-charge is not present, or the data cannot be collected for any other reason, the enumerator teams will coordinate and reschedule the visit. If, however, the officers-in-charge refuse to participate in the study, their non-response along with their reason for refusal will be recorded, and the facility will be replaced using random sampling from the required strata.

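### For any directly mapped item that is also in the advance questionnaire, Objective 1 measures mode plus preparation, not mode alone

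*Protocol article*

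**What the plan says.** Study objectives and contributions limits Objective 1 to questions that are the same in both surveys and states: "By keeping questions the same and varying only the administration mode, we can effectively isolate and examine the mode effect".

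Indicator mapping widens the term in one respect. Items with the same wording that are checked by observation in person still count as directly mapped, because "we consider in-person verification as a component of the mode effect". Preparation of answers is not mentioned there.

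Data collection procedures describes different conditions for the two surveys:

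- **In person.** "The advance questionnaire is a subset of the comprehensive in-person HFA and comprises of questions that require reference to facility data records". It is shared at least two weeks before the visit, with the stated purpose of "allowing respondents to prepare responses, thereby saving time and improving data quality on the day of data collection". One week before the visit the team calls again to "confirm the date of the first visit and request completion of the advance questionnaire".
- **Phone.** The survey is designed as a 30 to 45 minute interview "requiring no preparation by the officer-in-charge". It may begin on the first call or be scheduled for later.

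The section on Objective one analyses the directly mapped items by percent agreement, Cohen's kappa and PABAK. It does not separate items that are in the advance questionnaire.

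**The concern.** The article's own account is that preparation improves the data. An item that is prepared for one survey and not for the other is thus collected under two conditions that differ in expected accuracy, whatever the channel. Disagreement on such an item could come from the telephone, from the lack of preparation, or from both, and the planned statistics cannot tell these apart.

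The article applies this reasoning elsewhere. Indicator mapping keeps indirectly mapped items out of Objective 1 because a difference there might not be due to mode alone. A directly mapped item with one-sided preparation has the same weakness.

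Preparation also differs from verification. Verification needs someone on site, whereas a list of questions can be sent ahead of a phone call. If preparation explains a low kappa, the phone survey might be repaired by asking respondents to have their records at hand. If the telephone explains it, that would not help. The distinction matters because the article intends to use the results to refine the phone instrument before wider roll-out and to say which domains need in-person collection.

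**Working it through.** The plan states no figure for this point, so there is none to reproduce. The check has three parts.

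**1. How many items could be affected.** The article does not say which directly mapped items are in the advance questionnaire. S1 Appendix, which holds the item-by-item mapping, is not among the material reviewed. The lower bound is 0. The upper bound is every direct item: 22 by the printed total of Table 1, or 0 + 11 + 6 + 0 + 3 + 1 + 4 = 25 by its module rows. The two examples of direct items in the text (main electricity source, private toilets) do not look record-based. Some human resources items (6 direct) may be, but the article does not say so.

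**2. Whether the phone answer is really unprepared.** Take the advance questionnaire as shared 14 days or more before the visit, and the two surveys as at most 14 days apart, which Timing of survey administration calls ideal. The earliest phone call is then at day −14 relative to the visit, and the questionnaire has been shared by day −14. Every phone call falls on or after the day of sharing, even in phone-first facilities. In the half of facilities visited in person first, the record-based questions have been answered before the phone call. Preparation may therefore carry over to the phone in either arm, to an unknown extent.

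**3. Illustrative size.** Assumptions, none from the article: a binary item with true prevalence p = 0.90; symmetric error rates e₁ in person and e₂ by phone; errors independent given the truth; no mode effect as such.

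- Agreement: Po = (1 − e₁)(1 − e₂) + e₁e₂
- Share answering yes: mⱼ = p(1 − eⱼ) + (1 − p)eⱼ
- Chance agreement: Pe = m₁m₂ + (1 − m₁)(1 − m₂)
- Kappa = (Po − Pe)/(1 − Pe); PABAK = 2Po − 1

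With e₁ = 0.02, m₁ = 0.882 + 0.002 = 0.884.

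| Phone error e₂ | Po | m₂ | Pe | Kappa | PABAK |
|---|---|---|---|---|---|
| 0.02 | 0.9608 | 0.884 | 0.7949 | 0.81 (strong) | 0.92 (almost perfect) |
| 0.06 | 0.9224 | 0.852 | 0.7703 | 0.66 (moderate) | 0.84 (strong) |
| 0.10 | 0.8840 | 0.820 | 0.7458 | 0.54 (weak) | 0.77 (moderate) |

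For the last row, kappa = (0.8840 − 0.7458)/(1 − 0.7458) = 0.1382/0.2542 = 0.54. The middle row is what results if in-person-first facilities answer the phone with 2% error and phone-first facilities with 10%: (0.02 + 0.10)/2 = 0.06. The grades are those in the section on Objective one.

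The bias can also run the other way. If a phone respondent simply repeats the answers already prepared for the visit, the errors are shared rather than independent, Po = 1 and kappa = 1. That is above the 0.81 that two independent answers with 2% error would give.

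**The case against.** The strongest reply is that the article treats mode as a package. It says openly that verification belongs to the in-person mode, and preparation is part of the in-person procedure in the same sense. Strengths and limitations adds that fidelity to the two instruments as they will be used was a priority, so the comparison as fielded is the one of practical interest. That is a fair defence of the comparison. It does not rescue the claim that nothing but mode varies, because the article names verification and not preparation.

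A second reply is that nothing shown proves any Objective 1 item is affected. Directly mapped items were commonly those whose in-person form already suited the phone, and lengthy or detailed items were typically made indirect. This stands: the overlap may be small or nil, and the point is conditional on it.

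A third is that the order of the surveys is randomized and results will be compared by order. This helps in part. The comparison addresses priming by the earlier survey, but the in-person survey has its advance questionnaire in both arms, so order alone cannot isolate the effect of preparation.

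A reader might infer that phone respondents always answer from memory, that the contrast is equally large in either order, and that kappa drops two grades. The documents do not support this. Requiring no preparation does not forbid looking at a record, calls can be scheduled, questions can be delegated to other staff, and the advance questionnaire may already be in hand. The two-grade fall needs 10% phone error in every facility; with an average of 6% it is one grade.

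**Conclusion.** The point holds in conditional form. The article claims that Objective 1 varies only the mode, while its procedures also vary preparation for record-based questions. For any direct item in the advance questionnaire, the agreement statistics therefore estimate a mixture.

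The number of such items lies between 0 and all direct items. The direction is not fixed: unprepared phone answers would lower agreement, and carry-over from the advance questionnaire could raise it. Under the assumed error rates at 90% prevalence, kappa would be about 0.66 to 0.54 instead of 0.81, and PABAK 0.84 to 0.77 instead of 0.92. These figures show that a shift of one or two grades is possible without any effect of the telephone. They are not estimates for this study.

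The documents do not support concluding that Objective 1 as a whole is invalid, or that the overlapping items must be dropped. The defect is one of attribution, and it can be handled in reporting.

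**What to change.** 1. Flag in S1 Appendix each directly mapped item that is also in the advance questionnaire. If there are none, one sentence saying so closes the point.
2. Report the Objective 1 summary with and without the flagged items, and by survey order. Label the flagged items as mode plus preparation.
3. Qualify the wording in Study objectives and contributions that only the administration mode varies, so that it acknowledges preparation for these items.
4. Keep the flagged items in Objective 2, where agreement with the in-person standard is the question whatever the reason for a difference.
5. Where still feasible, record for each facility whether the advance questionnaire had been received or completed before the phone call.

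Steps 1 to 4 need no new data. They cost one flag per item, one extra split table and a sentence of text. The downside is fewer items in the restricted mode-effect summary. Step 5 can be kept as field-team tracking data, which avoids adding questions to instruments that have already been field-tested and back-translated.

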#### Timing of survey administration.

The comprehensive in-person HFA and the rapid phone-based HFA will be conducted as close in timing as possible, ideally within a two-week period for each health facility. The close timing of the surveys minimizes the risk of external factors (for example, a health facility receiving new medical supplies) impacting the data recorded in each survey and will ensure a more reliable comparison. However, there is a risk that conducting both surveys too close will introduce respondent fatigue that might affect results. Therefore, the order of the surveys for each health facility will be randomized to control for some of the real changes that may occur due to the order, with 50% of facilities receiving the rapid phone-based HFA first and 50% of the facilities receiving the comprehensive in-person survey first. This will allow for a more robust analysis. It will also allow us to conduct a longitudinal analysis of responses for the rapid phone-based HFA and the comprehensive in-person HFA in each facility to identify possible confounding effects depending on which survey the facility receives first. We would expect this to be a possibility especially in facilities that receive the in-person survey first, as respondent recall may be primed by the recent in-person verification of survey items and therefore, respondents may answer the rapid phone-based HFA with greater validity.

### Data analysis

Analysis will be conducted on a paired sample of each matched health facility that participated in both surveys.

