Taken together, these objectives will demonstrate whether the rapid phone-based HFA can approximate the results of the comprehensive in-person HFA for a select subset of facility-level indicators. As phone-based data collection in LMICs is a rapidly evolving field with growing interest following the COVID-19 pandemic, publication of this protocol aims to inform the broader scientific community of this undertaking and improve the transparency of our subsequent analysis against the study design articulated below.

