#### Sampling.

The sampling methodology for both surveys is designed to be representative of the PHC health facilities in Tajikistan at the national and oblast (region) levels. Since the role of private sector in providing PHC services is minimal in Tajikistan, the sample frame consists of all public PHC health facilities in the country comprising of- City and District Health Centers (family medicine departments), Rural Health Centers, and Health Houses. The sample was stratified across all oblasts. To obtain quality results from the comparison of the rapid phone-based HFA and the comprehensive in-person HFA, each survey will be conducted in the identical sample of 500 facilities described in Table 2.

**Table 2 pone.0309570.t002:** Sample for the rapid-phone based and comprehensive in-person HFAs.

		# Facilities	# Selected
Oblast	Dushanbe	15	15
	Sughd	616	151
	Khaktlon	1,123	150
	Gorno-Badakhshan Autonomous Region	227	84
	Districts of Republican Subordination	713	100
Type	City Health Center	41	41
	District Health Center	53	53
	Rural Health Center	895	214
	Health House	1,705	192
**TOTAL**		**2,694**	**500**
		

The enumerators will obtain verbal consent for the rapid phone-based HFA and written consent for the comprehensive in-person HFA from the respondents before starting the survey. If a respondent declines to participate, the reason for their refusal will be documented, and the facility will be replaced by a facility from the same strata whenever available. In the event of a non-response, health facilities will be replaced from a “replacement list” curated from the sample frame for each survey, following the same protocol of random sampling selection. Furthermore, in the event of a non-response, replacements for the two surveys will be done independently. This means that if a facility does not participate in the rapid phone-based HFA and needs to be replaced with another health facility, it will not be simultaneously replaced in the comprehensive in-person HFA, and vice-versa, unless the non-participation is due to the closure of the facility. As a result, the final samples may differ slightly due to varying response rates.

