#### Objective two: concurrent criterion validity analysis.

This objective focuses on concurrent criterion validity – the extent to which a new measurement technique agrees with a gold standard when the assessments are undertaken at approximately the same time. Both the “directly mapped” and the “indirectly mapped” indicators will be dichotomized to understand the differences in the results between the two surveys with the comprehensive in-person HFA being the gold standard. Sensitivity and specificity will be used to assess whether each indicator meets the predefined validation threshold of 0.7. This has been chosen as the validation threshold because of the specific intent to use low cost, high frequency surveys to generate timely signals as a complement to, rather than replacement for, periodic in-person surveys which are still needed for their depth, comprehensiveness, and rigor. We will also compare results stratified by direct versus indirect indicators and by survey domain (e.g., infrastructure, human resources) to identify any differences.

In addition, regression analysis will be conducted to assess whether sensitivity and specificity are associated with any of the seven domains of the rapid phone-based HFA, facility characteristics, respondent characteristics and potentially enumerator characteristics and timing between the two surveys. Sensitivity checks will also be conducted to see if the duration of time between the two surveys is correlated with the discordant answers.

Regression analysis will also be conducted to identify any variations in the findings that can be attributed to facility characteristics. Subgroup analysis will be conducted based on (1) oblast, (2) rural versus urban, and (3) facility type to identify if any underlying, facility characteristics influence the reliability and validity of the rapid, phone-based HFA results. This will identify whether validity is different in particular sub-groups. For example, the rapid, phone-based HFA may have improved validity in smaller facilities where one respondent is likely to be familiar with all the tracer items and could be more challenging in a larger facility with multiple departments.

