#### Objective three: non-response rate.

Although both surveys will initially include the same sample of 500 facilities, we expect that the final samples for each HFA will differ in the end due to varying non-response rates. A simple-t test will be used to assess whether there is a significant difference in the response rates between the rapid phone-based HFA and the comprehensive in-person HFA. Balance tests will also be used to assess whether the characteristics of the final sample of included facilities (the original sample plus any replacements) for the comprehensive in-person HFA and the rapid phone-based HFA sample remain similar across both surveys. Finally, we will document any issues with phone service coverage and the ownership of mobile phones by facilities and respondents, as well as any reported instances of costs to the recipient.

In case a significant difference is found in response rate or sample characteristics, regression analysis will be used to assess associations with discordance in survey completion. This will be done by creating a binary variable to indicate whether the comprehensive in-person HFA was completed in a health facility, while the rapid phone-based HFA wasn’t. This binary variable will then regressed on facility characteristics and whether the rapid phone-based HFA was initiated before or after the comprehensive in-person HFA. Since the non-response rate is expected to be higher for the rapid phone-based HFA, this analysis will only be done for health facilities which complete the comprehensive in-person HFA but not the rapid phone-based HFA.

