More broadly, findings from this study will be used to provide measurement and methodological guidance for HFAs. The findings will provide novel insights on the complementarities of various methods, which HFA domains and sub-domains can be administered via phone with high reliability and validity, and which HFA domains are likely to require in-person administration or other verification approaches. It is possible that the findings could be robust enough to generate correction factors for phone-based surveys that can be applied to approximate in-person measures in contexts where traditional data collection approaches are not possible (such as during health emergencies or conflict-impacted areas). Finally, the findings on response rates will be published to inform future implementation guidance on the feasibility of different methods of data collection given HFA operational constraints and measurement needs in different contexts and when each method is likely to be particularly useful.

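### Objective three never relates phone non-response to the indicators being validated, so the study cannot fully answer its own question of what bias the phone survey introduces

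*Protocol article*

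**What the plan says.** All references are to the protocol article.

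- **Aim.** The Introduction asks whether a phone survey can measure what in-person assessments measure, and what bias it brings. Study objectives and contributions says that, taken together, "these objectives will demonstrate whether the rapid phone-based HFA can approximate the results of the comprehensive in-person HFA".
- **Sample.** Under Sampling, "each survey will be conducted in the identical sample of 500 facilities". Facilities that refuse are replaced from the same stratum where possible, other non-responders from a randomly drawn replacement list, and "replacements for the two surveys will be done independently".
- **Reliability and validity.** The Data analysis section states: "Analysis will be conducted on a paired sample of each matched health facility that participated in both surveys". Under Objective two, "Sensitivity and specificity will be used to assess whether each indicator meets the predefined validation threshold of 0.7".
- **Expected non-response.** Objective three expects more of it by phone. Study objectives and contributions names connectivity and time constraints as causes. Data collection procedures says of the repeated contact attempts: "This will be particularly important for remote facilities with low phone connectivity, where the respondent may have sporadic access to a stable phone network".
- **Planned non-response analysis.** Objective three has a t-test of response rates, balance tests on the final samples including replacements, and a record of phone coverage and ownership problems. If a rate or characteristic differs significantly, an indicator of in-person completion without phone completion is modelled: "This binary variable will then regressed on facility characteristics and whether the rapid phone-based HFA was initiated before or after the comprehensive in-person HFA".
- **Possible later use.** Strengths and limitations raises one further possibility, that the results might "generate correction factors for phone-based surveys that can be applied to approximate in-person measures in contexts where traditional data collection approaches are not possible".

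**The concern.** Paired sensitivity and specificity say whether an answer is right once a facility has given one. A phone survey reproduces the in-person result only if, in addition, the facilities that answer resemble those that do not on the item in question. The causes of phone non-response that the article names (remoteness, weak networks, lack of time) could plausibly go with the infrastructure, staffing and supply items under validation. That link is not shown in the document.

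Objective three is where this should be picked up, but each of its parts looks elsewhere:

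- The t-test concerns rates only.
- The balance tests use final samples that include replacements, partly from the same strata. Balance on stratum variables is therefore partly restored by design, and differences in availability within a stratum can stay hidden.
- The regression depends on a significance test, and its stated predictors do not include the indicator values. The last sentence of the section also confines it to facilities that completed the in-person survey but not the phone survey. Taken literally, the outcome is then constant. The likely intention is to model only that direction of discordance, but the text should say so.

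At stake is the planned guidance on which domains can be collected by phone. An indicator could pass the 0.7 threshold comfortably while the phone estimate still differs from the in-person one, and no stated statistic would show the difference.

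**Working it through.** The article gives no non-response rate and no figure for this bias, so there is nothing to reproduce. The following uses assumed values.

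**Inputs.** 500 facilities (Sampling, Table 2). Assumed: true availability p; phone response a where the item is present and b where it is absent; phone answers perfect (sensitivity = specificity = 1); every facility completes the in-person survey; one stratum, no replacement, no weights.

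**Formulas.** Response rate r = p·a + (1 − p)·b. Availability among phone responders q = p·a / r. Bias = q − p.

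| p | a / b | r | q | Bias (points) |
|---|---|---|---|---|
| 0.80 | 0.90 / 0.90 | 0.90 | 0.800 | 0 |
| 0.80 | 0.95 / 0.85 | 0.76 + 0.17 = 0.93 | 0.817 | +1.7 |
| 0.80 | 0.90 / 0.70 | 0.72 + 0.14 = 0.86 | 0.837 | +3.7 |
| 0.80 | 0.90 / 0.50 | 0.72 + 0.10 = 0.82 | 0.878 | +7.8 |
| 0.60 | 0.95 / 0.85 | 0.57 + 0.34 = 0.91 | 0.626 | +2.6 |
| 0.60 | 0.90 / 0.70 | 0.54 + 0.28 = 0.82 | 0.659 | +5.9 |
| 0.60 | 0.90 / 0.50 | 0.54 + 0.20 = 0.74 | 0.730 | +13.0 |

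If b exceeds a, the sign reverses.

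**Would a correction from the paired statistics remove it?** Take p = 0.80 and a/b = 0.90/0.70, now with sensitivity = specificity = 0.85. Observed phone prevalence is 0.85 × 0.837 + 0.15 × 0.163 = 0.736. The usual correction, (observed + Sp − 1) / (Se + Sp − 1), gives (0.736 − 0.15) / 0.70 = 0.837. It returns q, not p.

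**Can the planned data show it?** In the same case, phone non-responders number 0.14 × 500 = 70. Their availability is 0.80 × 0.10 / 0.14 = 0.571, against 0.837 in responders, a gap of 27 points. SE = √(0.837 × 0.163 / 430 + 0.571 × 0.429 / 70) = 0.062, about 6 points. As a check, non-response share × gap = 0.14 × 0.266 = 3.7 points, the bias in the table.

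**Power** to detect 80% in responders against 60% in non-responders (two-sided 0.05, 500 facilities, unweighted):

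| Phone non-response | Non-responders | Power |
|---|---|---|
| 5% | 25 | 0.64 |
| 10% | 50 | 0.86 |
| 20% | 100 | 0.98 |
| 30% | 150 | 0.99 |

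**The case against.** **The paired set is not an error.** A reader might infer that restricting the analysis to pairs is the defect. It is not: agreement, sensitivity and specificity exist only where both answers exist, and objectives one and two ask about answers given. This stands in full.

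**Non-response has its own objective.** The overall conclusion rests on all three objectives together. This also stands, and it narrows the point to what objective three examines.

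**The covariates are not listed.** The article is condensed, and a full plan could include indicator values among the facility characteristics. This stands in part. The article does fix the type of predictor, the significance condition and the balance tests, and none of these names the indicators.

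**Safeguards are left out of the figures.** At least five contact attempts, scheduled callbacks and same-stratum replacement should reduce selection. Replacement helps where remoteness differs between strata. It does not help within a stratum, because a replacement that answers is itself a phone responder. In Dushanbe all 15 of 15 facilities are selected, so none is left as a replacement.

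**The direction is assumed.** A reader might infer that the phone survey will overstate availability. The document does not support that: time constraints could equally keep busier, better-equipped facilities from answering.

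**Correction factors are only a possibility.** A reader might infer that the planned factors are biased. No factor is planned and no construction is given, so only a conditional caution is justified.

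**In-person values are not complete.** They exist only for phone non-responders that complete the in-person survey, not for facilities that refuse both.

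**Conclusion.** The point holds in limited form. The paired analysis is correct for what it estimates, but its results are conditional on phone response, and no stated analysis links phone non-response to the indicators being validated. As written, the study could miss within-stratum selection on those indicators and so cannot fully answer its own question about bias.

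The size and direction are unknown. The figures of about +2 to +8 points at 80% availability rest on assumed response gaps of 10 to 40 points, with lower response where the item is absent, and they ignore replacement, weighting and in-person non-response. The 40-point gap is an upper illustration with no support in the document. The consequence is tempered because the phone survey is meant to complement in-person assessments, not replace them. The change is still worth making, since the data needed are already to be collected.

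**What to change.** - **Add to objective three.** Among original-sample facilities that completed the in-person survey, report for each mapped indicator the in-person prevalence (a) in all of them and (b) in those that also completed the phone survey. Give (b) − (a) with a confidence interval, whether or not the response-rate test is significant.
- **Regression.** Fit the non-completion model on all in-person completers, with phone completed or not as the outcome.
- **Labelling.** Describe the agreement, sensitivity and specificity results as conditional on phone response, and read them beside the non-response term when concluding which domains can be collected by phone.
- **Correction factors.** If any are ever derived from the paired statistics, state that they apply to phone responders only, or add the non-response term.

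The cost is some wording and one more table, with no new fieldwork. The term will be imprecise if few facilities fail to answer by phone, and it says nothing about facilities that refuse both surveys.
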